### Intervention condition: implementation of STA OP!

A comprehensive training program for healthcare professionals will be organized to implement the STA OP!-protocol. Healthcare professionals participating in this study will be nursing home physicians, psychologists, occupational therapists and registered or certified nurses (CNA/RN). In most of the nursing homes the majority of the registered or certified nurses will have relatively low educational levels 1, 2 or 3, which in Dutch is called 'verzorgenden' or 'helpenden'. Nurses and physicians who only work night shifts will be excluded from this study. Only the CNA/RN (levels 3, 4 or 5) is authorized to start the protocol.

Nursing home staff from all experimental units will be trained in the stepwise working method of the STA OP!-protocol in five meetings lasting three hours each. The team members will be taught enhanced physical and affective assessment skills that target needs commonly found in people with advanced dementia. A collaborating training centre, with very experienced trainers, will provide the STA OP!-training. These trainers are advanced practice nurses or have other medical backgrounds and have specific professional expertise regarding dementia, pain and discomfort.

In the sessions it will be discussed how nursing home staffs can recognize symptoms related to pain and affective discomfort, and how they can communicate with each other about these symptoms. In the first meetings the initial two steps of the STA OP!-protocol will be discussed, while in the follow up meetings the focus is on the last three steps.

The steps of the STA OP!-protocol are outlined in the following section. Each step is systematically written down in the STA OP!-protocol, which serves as a template for nurses and nursing home physicians to use the stepwise approach in practice (see also Figure 1). How much time it takes to decide to proceed to the subsequent step, depends on the specific interventions chosen. However, in general when effects are lacking or when they are limited, this should not take longer than one week.

Other healthcare professionals can be consulted at any time and at each step in the process.

#### • Step 0: Basic care needs

The nurse assesses whether or not basic physical care needs are fulfilled. Basic care needs concern, for instance hunger, thirst, a need for glasses, hearing aids or toileting.

#### • Step 1: Physical needs assessment (nurse and nursing home physician)

In addition to a brief physical nursing assessment, the nurse will also fill out an observational pain instrument (PACSLAC-D). If these assessments are negative, a nursing home physician (or if available a nurse practitioner) performs a more comprehensive physical assessment to find other probable physical causes, such as inflammation, infection, acute illness or a chronic condition possibly responsible for the observed behaviour.

For those residents already using pain medication or psychotropic drugs and still have behavioural symptoms possibly related to pain or affective discomfort, the nursing home physician will also assess whether the medication given is in accordance with the guidelines of the World Health Organization (WHO) and Verenso (the Dutch association of nursing home physicians) (also see Step 4 and 5).

#### • Step 2: Affective needs assessment

By using a needs-oriented and tailored approach, the nurse assesses possible problems regarding environmental stress, a possible imbalance between sensory stimulating and sensory calming activities, or a lack in meaningful human interactions. The psychologist working in the nursing home can be consulted at this step.

#### • Step 3: Non-pharmacological comfort interventions

In this step non-pharmacological comfort interventions will be conducted and implemented, in line with the personal history of the resident. Examples of comfort interventions are soothing, supportive verbal communication, supportive touch, and sensory stimulation by music, nice smells or soft materials. A study by van Weert [46] showed that these types of comfort interventions are effective in reducing discomfort in nursing home residents.

#### • Step 4: Trial of analgesics

In this step of the protocol the nursing home physician is advised to prescribe a trial of analgesics according to the validated pain ladder, developed by the World Health Organization [47]. Specific guidelines for use in the elderly are given to each participating nursing home physician in a training session, and similarly for physicians working in control and intervention units.

#### • Step 5: Consultation of relevant other disciplines (e.g. psychiatrist) and/or trial of prescribed psychotropic drugs

In the protocol and training sessions, nursing home physicians are instructed to use the guidelines of the Dutch association of nursing home physicians (Verenso) for prescribing psychotropic medication [48]. The Verenso-guidelines clearly describe how and when psychotropic drugs are beneficial for dementia patients. In general, it is believed that this medication is only indicated for specific symptoms and for a fixed period of time.

In the training session it is also discussed that in general, a subsequent protocol step is needed when targeted assessments are negative, or when the symptoms related to pain or affective discomfort have not been reduced sufficiently by the targeted interventions.

During the training, the nurses and nursing home physicians start using the STA OP!-protocol for the residents who have been assessed by the blinded research assistants at pre-test (in week 0) as having a CMAI, NPI-NH and/or MDS-RAI pain scale score above the threshold. It can be expected that the STA OP!-protocol will also be used in other residents showing behavioural symptoms of pain or affective discomfort (outside the measurement weeks): this is allowed and will be registered. To promote the use of the protocol in practice, a focus group will be formed within the units of the institution. The researcher performs site-visits ones a week on the experimental units and provides nurses and nursing home physicians feedback on their use of the STA OP!-protocol in particular residents and answers their questions regarding pain or affective discomfort.

### Therapy compliance

In the proposed study, therapy compliance is taken into account by the fact that the research assistant/advanced practice nurse who visits the experimental units once a week will have ample and structured focus on the actual use of the protocol in practice. The site-visits will include assessment whether the protocol is adequately used, the patient assessments performed adequately, if planned non-pharmacological interventions are executed and if prescribed analgesics or psychotropic drugs are indeed administered and used. The daily logs from the units will provide additional information on the actual use of the protocol, as well as reports from interdisciplinary meetings.

### Instruments

Various baseline measurements, primary outcome measures, secondary outcome measures, demographic-, and control variables can be distinguished in this study. The instruments are observational instruments, which are filled in by a contact nurse. In addition, video recordings will be made for analysis by independent blinded observers on pain and discomfort (see Table 1).

### Primary outcomes

Primary outcomes measures include symptoms of challenging behaviour and/or pain.

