**Methods/Design:**

The study is a cluster randomized controlled trial in 168 older people (aged >65 years) with mild or moderate dementia living in nursing homes. The clusters, Dutch nursing homes, are randomly assigned to either the intervention condition (training and implementation of the STA OP!-protocol) or the control condition (general training focusing on challenging behaviour and pain, but without the step-wise approach). Measurements take place at baseline, after 3 months (end of the STA OP! training period) and after 6 months.

Primary outcome measures are symptoms of challenging behaviour (measured with the Cohen-Mansfield Agitation Inventory (CMAI) and the Neuropsychiatric Inventory-Nursing Home version (NPI-NH)), and pain (measure with the Dutch version of the Pain Assessment Checklist for Seniors (PACSLAC-D) and the Minimum Data Set of the Resident Assessment Instrument (MDS-RAI) pain scale). Secondary outcome measures include symptoms of depression (Cornell and MDS-RAI depression scale), Quality of Live (Qualidem), changes in prescriptions of analgesics and psychotropic drugs, and the use of non-pharmacological comfort interventions (e.g. snoezelen, reminiscence therapy).

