#### Research aims and hypotheses

The purpose of this study is to assess the effects of the stepped wise Dutch version of the STI (STA OP!) versus a non-stepped wise approach to pain and behavioural symptoms.

Research questions:

1. Does STA OP! affect the number of symptoms of pain or challenging behaviours in nursing home residents differently (compared to usual care)?

2. Does the use of STA OP! lead to a change in use of analgesics and psychotropic drugs?

3. Does the use of STA OP! result in a change in use of non-pharmacological comfort interventions?

4. Does the use of STA OP! lead to a change in depressive symptoms and the quality of life in advanced dementia patients?

5. Is the effect of intervention moderated by the Apolipoprotein Epsilon 4 (Apo-E4) status of the patient?

It is hypothesized that implementation of the STA OP!-protocol will lead to less pain, fewer expressions of challenging behaviour, improved mood, higher use of pain medication and a lower use of antipsychotics (resulting in a decrease in side effects) with an increased use of non-pharmacological comfort interventions. However, we will also be able to identify findings of outcomes that reverse the direction of the hypothesis.

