## Methods

### Study design

The study is a cluster randomized controlled trial. The clusters, Dutch nursing homes, are randomly assigned to either the intervention condition (implementation of the STA OP!-protocol) or the control condition (general training without the step-wise approach). Measurements take place at baseline, after 3 months (at the end of the STA OP!-training period) and after 6 months.

The study is single blinded i.e. the researcher will know the condition, while the research assistants performing the measurements and the persons analysing and score the video registrations are blinded. They will also not be informed about the specific research questions and conditions.

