### Sample size and power analysis

One of the primary outcome measures in this study is the CMAI, a behavioural observation scale with 29 behavioural items. Each item may be scored between 1 and 7, depending on the frequency of existing symptoms. The range on the CMAI is 29-203. In Dutch nursing homes the median is 44 [44]; there is no normal distribution, but the distribution of the change is more or less normally distributed. The standard deviation of difference scores (difference of 4) is 13. The expected difference is however larger (at least 10 points). To detect a 15% difference between the intervention (STA OP!-protocol) and control condition with an α = .05 and β = .80, 56 residents will be required. However, in cluster randomization, a design effect should be taken into account; clustering of items (consistency of CMAI items [ICC] among residents in a unit is .10) and also the effect of large differences in sample sizes per cluster enhances the design effect [45].

In this study the design effect was estimated at 1.5; So, 1.5 × 56 = 84 residents (after 4 weeks) will be needed in total to detect a 15% difference with an α = .05 and β = .80. However, we expect a 50% dropout due to non-response and loss to follow-up, i.e. we will need 168 patients in total; 84 in the intervention- and 84 in the control group.

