#### Pain

Symptoms of pain will be measured with the pain scale of the Dutch version of the Minimum Data Set of the Resident Assessment Instrument (MDS-RAI) [34] and with the Pain Assessment Checklist for Seniors (PACSLAC-D) [37]. The MDS contains two pain items: 'pain frequency' and 'pain intensity'. In the MDS, pain frequency is coded as no pain (0); less than daily pain (1); and daily pain (2) in the last 7 days. Pain intensity is categorized as no pain; mild pain (0); moderate pain (1); and severe pain (2, times when pain is horrible or excruciating) in the last 7 days. The product of intensity and severity in this study has to be ≥2 to be defined as clinically relevant pain.

The validity and precision of pain measurement with MDS items have been established against the Visual Analogue Scale in a study involving 95 US nursing home residents [34]. The definition of pain in the MDS is ''Pain refers to any type of physical pain or discomfort of the body. Pain may be localized to one area, or be more generalized. It may be acute or chronic, continuous or intermittent (comes and goes), or occur at rest with movement. The pain experience is very subjective; pain is whatever the resident says it is." Coding instructions are ''Code for the highest level of pain present in the last seven days" [54].

The PACSLAC-D is a brief and manageable version of the Pain Assessment Checklist for Seniors with Limited Ability to Communicate [35] in Dutch that was developed by Zwakhalen [37], with a three component solution including 24 items. This version had high levels of internal consistency for the complete scale (Cronbach's alpha range 0.82-0.86) and for all subscales (alpha range 0.72-0.82).

Both the pain scale of the MDS-RAI and the PACSLAC-D will be assessed by the contact nurse of a particular resident at baseline and after 3 and 6 months.

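### Four scales at two follow-up visits are all primary with no lead scale or visit and inconsistent *and*, *or*, *and/or* wording, while the sample size covers one unadjusted CMAI comparison only

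*Protocol article*

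**What the plan says.** **Which outcomes are primary.** The abstract (Methods/Design) states "Primary outcome measures are symptoms of challenging behaviour (measured with the Cohen-Mansfield Agitation Inventory (CMAI) and the Neuropsychiatric Inventory-Nursing Home version (NPI-NH)), and pain", and gives PACSLAC-D and the MDS-RAI pain scale as the pain measures. Table 1 lists the same four scales under primary outcome. The section Primary outcomes reads "Primary outcomes measures include symptoms of challenging behaviour and/or pain". Research question 1, under Research aims and hypotheses, joins pain and challenging behaviour by *or*.

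**When they are measured.** Study design: "Measurements take place at baseline, after 3 months (at the end of the STA OP!-training period) and after 6 months". The Pain section has the resident's contact nurse rate the two pain scales at all three of these times. Table 1 shows nurse ratings of all four scales at both follow-ups. It also shows a video rating of PACSLAC-D at baseline and 3 months, but not at 6 months. Neither follow-up visit is called primary.

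**What the trial is sized on.** Sample size and power analysis opens with "One of the primary outcome measures in this study is the CMAI". It continues "The standard deviation of difference scores (difference of 4) is 13", expects a difference of at least 10 points, and concludes "with an α = .05 and β = .80, 56 residents will be required". A design effect of 1.5 and a 50% dropout take this to 84 and then 168. The 84 is described as the number needed at four weeks, which is not a scheduled assessment.

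**How it is analysed.** Statistical analyses plans multilevel models. It does not say whether each scale yields one effect over both visits or one effect per visit.

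**The concern.** Which outcome and visit are primary, and whether the two domains must both succeed or either will do, is protocol content. The article addresses it in three places with three connectors, and they imply different criteria. *And* can mean that both domains must show an effect. *Or* and *and/or* allow one domain to carry the claim.

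The sample size then behaves as if there were a single primary comparison, the CMAI at 5%, while that section itself calls the CMAI only one of several. It does not settle the visit either, because the time it mentions is not in the schedule.

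Two things are at stake. If any one scale may count, the chance of a false primary success exceeds the stated 5%. If alpha is later divided to prevent this, the stated 80% power no longer holds for the planned number of residents.

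**Working it through.** **1. The plan's own figure.** Inputs from Sample size and power analysis: difference 10 points, SD of change 13, alpha .05, and the figure given for β read as power .80. Sidedness is not stated. I take two-sided, because the authors write "we will also be able to identify findings of outcomes that reverse the direction of the hypothesis".

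Two-sample t-test with standardised difference 10/13 = 0.77:

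- Required per arm: 27.5, rounded up to 28, so 56 in total. This matches the article. The normal approximation gives 27 per arm, 54 in total.
- 56 × 1.5 = 84, and 84 / (1 − 0.5) = 168. Both match.

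Reading the 15% difference as 15% of the median of 44 (6.6 points) would need 122 residents by the normal approximation, so the 56 rests on 10 points. It also rests on one comparison at an undivided .05.

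**2. Number of comparisons.** Four scales with one effect each give 4 tests. Four scales at two visits give 4 × 2 = 8. The video-rated PACSLAC-D at 3 months would be a ninth. I leave it out.

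**3. Chance of at least one false success if any one counts.** For k independent tests at 5% this is 1 − 0.95^k:

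- k = 4: 1 − 0.8145 = 18.5%
- k = 8: 1 − 0.6634 = 33.7%

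For correlated tests it was simulated with 1,000,000 draws of multivariate normal test statistics, two-sided 5%. The correlations are assumptions.

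| Common correlation | 4 tests | 8 tests |
|---|---|---|
| 0 | 18.5% | 33.7% |
| 0.3 | 17.4% | 30.0% |
| 0.5 | 15.6% | 25.1% |
| 0.7 | 13.0% | 19.1% |

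With separate correlations for scales and visits, eight tests give 29.9% (scales 0.3, visits 0.5), 26.9% (0.5, 0.5) and 24.9% (0.5, 0.7), all inside the same range.

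If all four scales had to succeed, the error would not exceed 5%. The chance of joint success would then be no higher than the power of the weakest scale, and the CMAI calculation would not describe it.

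**4. What the 80% power covers.** The planned 84 evaluable residents divided by the design effect of 1.5 are worth 56, or 28 per arm. Power of the t-test for 10 points with SD 13:

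| Alpha for the CMAI test | Power |
|---|---|
| .05 | 81% |
| .05/4 = .0125 | 62% |
| .05/8 = .00625 | 52% |

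The normal approximation gives 82%, 65% and 56%. By that approximation, restoring 80% power after a split would take 76 residents (four tests) or 88 (eight) before inflation. That is 76 × 1.5 / 0.5 = 228 or 88 × 1.5 / 0.5 = 264 enrolled, against 168.

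**The case against.** A reader might infer that the protocol sets eight primary comparisons with a rule that any one suffices, and so carries a 25–34% false-positive rate as a fact. The article does not support that:

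- The Primary outcomes sentence lists the constructs measured. A similar *and/or* phrase describes residents' symptoms in the inclusion criteria. No passage says when the trial counts as positive.
- Eight separate tests are not stated. A multilevel model can give one effect per scale across both visits, which brings the figure to about 13–19%.
- No correlation is given. Eight tests at a correlation of 0.7 give about 19%, below 25%.

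It can also be said that the method of error control belongs in an analysis plan that is not shown, and that sizing on one of several primary outcomes is common and here disclosed.

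Most of this stands. The error figures must be conditional and the range wide, and the absence of an adjustment method is no finding. What it does not answer is that the article fixes four primary scales with no lead, leaves the visit open, and joins the domains in three ways. An analysis plan that resolved this by dividing alpha would undercut the article's own sample size.

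**Conclusion.** The point holds in conditional form. The primary outcome is not uniquely defined: there are four scales, two visits, no lead and three connectors. The stated 5% and 80% describe only one unadjusted CMAI comparison, at a visit the article does not identify.

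If success on any one primary scale is accepted, the chance of a false primary success is roughly 13–34%: 13–19% with one test per scale, 19–34% with one per scale and visit. This assumes two-sided 5% tests and correlations from 0 to 0.7. The power figures of 81%, 62% and 52% assume 10 points, SD 13, a design effect of 1.5, the expected 50% dropout and an equal split of alpha.

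This should be corrected. It does not by itself invalidate the design, because one sized outcome is already available to lead.

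**What to change.** - Name the CMAI total score at one stated, scheduled visit as the lead primary outcome, since it is the scale that was sized. Correct the four-week reference in the sample size section to that visit.
- Test one pain measure next in fixed sequence at 5%, only if the CMAI result is significant. Its rater and visit must match Table 1: nurse-rated PACSLAC-D if at 6 months; the blinded video-rated PACSLAC-D is possible only at 3 months.
- Make the remaining scales and the other visit secondary.
- Use one connector consistently in the abstract, research question 1 and the Primary outcomes section.

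The cost is protocol wording: no extra residents, and no extra recordings if the pain measure follows the existing schedule. The downside is that a confirmatory pain claim becomes conditional on the CMAI result. If the sponsor prefers several co-equal primary scales with alpha divided among them, the sample size has to be redone (see the enrolment figures in the working).

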#### Challenging behaviour

Symptoms of challenging behaviour will be measured with the Dutch version of the

Cohen-Mansfield Agitation Inventory (CMAI) [30,31,49,50], and with the Dutch version of the Neuropsychiatric Inventory-Nursing Home Version (NPI-NH) [51-53].

The CMAI was developed to assess agitation in nursing home patients [30,31]. It is more specific than general-purpose behaviour rating scales, which usually include self-care activities, cognition, and mood items. The CMAI uses a 7-point scale to assess the frequency (ranging from 'never' to 'several times an hour') of 29 behaviours commonly seen in nursing home residents. Behaviours are characterized in four clusters: verbally aggressive (e.g., directed at a person or object), verbally nonaggressive (not directed at a specific object or person), physically aggressive (directed), and physically nonaggressive (undirected). The total score is most commonly used to quantify behavioural disturbance. Professional caregivers, who are usually nurses or nursing assistants, assess this scale. The staffs are trained prior to using the instrument. Factor analysis has shown three basic dimensions underlying the 29 CMAI items: physical aggression, physical nonaggression, and verbal agitation. It is a reliable and valid instrument to measure behavioural symptoms in dementia patients [49,50].

The NPI-NH is a structured interview with a healthcare professional (CNA/RN). In this interview ten neuropsychiatric symptoms are assessed: delusions, hallucinations, agitation/aggression, dysphoria, anxiety, euphoria, apathy, disinhibition, irritability/lability. Screening questions are asked to determine whether behavioural changes are present. In the case of a positive answer, further questions are asked and the severity and frequency of the behavioural disturbances are determined. The Dutch version of the NPI has high inter-rater agreement and is found to be a valid rating scale for measuring a wide range of behavioural and psychological symptoms of dementia [51,52].

